## Background

Women with symptoms of preterm labour have long posed a diagnostic challenge for clinicians concerned with managing the risks of preterm birth when the reality is that most women will not deliver imminently [1]. Various prediction methods are available to direct interventions that delay or ameliorate the consequences of preterm birth (e.g. in-utero transfer, tocolysis, antenatal corticosteroids). However these interventions have psychological, economic and clinical implications if given unnecessarily.

In light of recent UK guidance to treat all women in threatened preterm labour (TPTL) prior to 30 weeks [2], most of these women are likely to be admitted. However, the majority of women presenting with symptoms of preterm labour will not deliver in seven days [1].

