### Randomisation

Randomisation is at the cluster level. Centres have been randomly allocated to receive either intervention or control. Due to there being an odd number of centres, seven sites were allocated to one group and six to the other. Minimisation of the randomisation list was not appropriate for this design but the imbalances between three levels of NICU facility at intervention and control sites were small (4:3, 3:2, and 0:1). TPTL rates were known for 10 sites and the difference between the average rates at control and interventions sites were within chance (72 and 89%).

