### Data analysis

#### Cluster randomised trial

Data analysis will follow the intention to treat principle, according to the planned intervention. Data will be analysed using Stata software Version 14 or later (StataCorp, College Station, Texas) to estimate the size and test for statistical significance of any effects of the intervention on primary and secondary, and analysis will be supervised by the trial statistician, [name]. A per protocol analysis will also be performed, excluding those who are incidentally admitted or treated for reasons unrelated to preterm labour. Treatment effects for binary endpoints will be expressed as risk ratios (relative risk) with 95% CIs, using binomial regression and adjusting for variables used in the minimization process. Risk differences will also be calculated for the primary endpoint. The analysis model will include a random effect for clustering and adjusted standard errors for clustering. Adjustments will also need to be made for differences between cluster populations, such as ethnicity and maternal age. Our primary outcome of inappropriate decisions will be measured per 1000 deliveries.

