### Implementing the QUiPP app intervention

In each phase, each cluster will recruit consecutive women with singleton or twin pregnancies presenting between 23^+ 0^ and 34^+ 6^ weeks presenting with symptoms of preterm labour. Eligible participants will be identified at labour ward and day assessment triage by the direct care team and local research support teams. Inclusion and exclusion criteria are defined above.

All sites will receive training on the use of the QUIPP App and management guidance prior to its introduction, and periodically throughout the trial at peaks of staff turnover. This training will be delivered by the trial team at different times and locations to suit each site, for example, at departmental audit meetings and staff induction. Training will be delivered via clinical vignettes which provide opportunity for the clinicians to use the app in a training environment. Aide-memoires such as lanyards and pens are provided to each site to encourage use of the app. The doctor/midwife assessing the woman inputs the gestation, previous history of late miscarriage or preterm birth, quantitative fetal fibronectin value and/or ultrasonic cervical length into the app and the app provides % risk of delivery within 1/2/4 weeks and before 30/34/37 weeks. The exact thresholds for admission or treatment are gestation-dependent and may need to be tailored to individual circumstances. However as a recommendation, our guidance will suggest a 5% risk of delivery within 7 days as threshold for antenatal corticosteroid administration, admission, and/or in-utero transfer. Ultimately however the management decisions following the knowledge provided by the QUIPP app will remain the clinicians’ responsibility. A feedback option is available on the app to directly contact the trial team with specific non-clinical queries. Incentives and competitions will also aim to increase recruitment for the qualitative recruitment.

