## Discussion

Management of TPTL has represented a clinical conundrum for decades. Intervention “just-in-case” results in many unnecessary admissions, women being transferred out of their local hospital unnecessarily and most women receiving unnecessary drugs, such as steroids and tocolytics. It also prevents appropriate transfers as neonatal cots are blocked unnecessarily, resulting in more dangerous ex-utero transfers. One reason for the current trend for over-treatment of TPTL is concern that the false-negatives any triage system entails. This study will determine the risks and benefits of limiting management and treatment to those most at risk of delivery.

The exact thresholds for admission or treatment are gestation-dependent, may need to be tailored to individual circumstances and will remain the clinicians’ responsibility. As a recommendation, our guidance will suggest a 5% risk of delivery within seven days as threshold for antenatal corticosteroid administration, admission, and/or in-utero transfer. A 5% threshold is equivalent to an odds of 5:95 which is 1:19. This estimates the harm of a missed imminent delivery (a false negative) is 19 times as great as the harm of overtreatment (a false positive). It was found to be an acceptable threshold for intervention in our Delphi survey of preterm birth specialists. In the context of national guidance which advocated more intervention and disregarded the risk of harm this incurs to the majority [2], this study’s comprehensive evaluation of the true clinical impact of the QuiPP app will determine and justify an appropriate threshold for TPTL intervention for the first time.

If, as we hypothesise, the QUIPP app improves selection of the appropriate women for admission and transfer, it will ensure that therapies known to reduce risk of preterm neonatal morbidities are offered to those who need them and reduce the associated maternal and fetal risks to women who do not. Conversely if a treat-all policy is justified, we can help define resource use and clinical need to inform policy makers. Beyond obstetrics, evaluating the impact of an app in an emergency setting, and our emphasis on balancing harms of over-treatment as well as under-treatment, make EQUIPTT a valuable contribution to translational medicine.

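### The adjustment statement gives ethnicity and maternal age as examples and cites minimisation variables that do not exist, but does not name gestation at presentation, which the protocol says shapes the admission decision

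*Protocol article*

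**What the plan says.** The Cluster randomised trial part of Data analysis plans binomial regression with a random effect for cluster, and makes two statements about covariates.

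- The model is fitted "adjusting for variables used in the minimization process". Yet the Randomisation section says "Minimisation of the randomisation list was not appropriate for this design", and reports the balance of NICU level and threatened preterm labour rate only as a description of the allocation obtained.
- "Adjustments will also need to be made for differences between cluster populations, such as ethnicity and maternal age".

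Gestation at presentation appears in neither. Elsewhere the article ties it to the decision that the primary outcome scores:

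- Background reports "guidance to treat all women in threatened preterm labour (TPTL) prior to 30 weeks [2], most of these women are likely to be admitted".
- The text on guiding management under Maternal risks gives gestational age as its example of what contributes to the decision.
- Implementing the QUiPP app intervention says "The exact thresholds for admission or treatment are gestation-dependent", and lists gestation as an input to the app. The Discussion repeats the point about thresholds.
- Data collection lists gestation at presentation among the key data for all patients at control and intervention sites.

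On policy, the Discussion adds: "Conversely if a treat-all policy is justified, we can help define resource use and clinical need to inform policy makers".

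**The concern.** Under Primary outcomes, a woman who is admitted and does not deliver within 7 days counts as inappropriately admitted. Background says that most symptomatic women do not deliver within 7 days and that most women before 30 weeks are likely to be admitted. On the article's own account, then, the control-arm rate of inappropriate admission should be higher at early gestations, which makes gestation a strong candidate prognostic covariate.

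The two covariates that are named are nowhere linked to the admission decision, and the third source is an empty set. With 13 clusters, the arms may differ by chance in the share of early presenters, and an unadjusted contrast carries that difference. A list tied to differences between cluster populations, with only examples given, also leaves room to choose covariates after the imbalances are seen.

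**Working it through.** **1. The planned sample size reproduces and is not in dispute.** Inputs from Sample size: 25% v 10%, intra-class correlation 0.030, 13 clusters, 580 women. Two-sided alpha 0.05 is stated only for the questionnaire and is assumed here. Sites are 6 control and 7 intervention.

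- Cluster size m = 580/13 = 44.6; design effect = 1 + (44.6 - 1) × 0.030 = 2.31.
- Effective sizes: (580 × 6/13)/2.31 = 116 and (580 × 7/13)/2.31 = 135.
- SE of the risk difference = √(0.25 × 0.75/116 + 0.10 × 0.90/135) = 4.8 points.
- Power on t with 11 degrees of freedom = 81.5%, against the stated 80%.

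**2. Effect of a difference in gestation mix.** The article gives neither the share of women presenting before 30 weeks (s) nor their inappropriate-admission rate (p). Assume s = 30-40% and p = 40-60%, and hold the overall control rate at the planned 25%.

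- Rate from 30 weeks = (0.25 - s × p)/(1 - s); gap = p minus that rate.
- Shift in the unadjusted contrast = (arm difference in early share) × gap.
- Share of control-arm outcome variance explained, R² = s(1 - s) × gap²/(0.25 × 0.75).

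| s | p | Rate from 30 weeks | Gap (points) | Shift, 10-point difference | Shift, 5-point difference | R² |
|---|---|---|---|---|---|---|
| 30% | 40% | 18.6% | 21.4 | 2.1 | 1.1 | 0.05 |
| 30% | 50% | 14.3% | 35.7 | 3.6 | 1.8 | 0.14 |
| 30% | 60% | 10.0% | 50.0 | 5.0 | 2.5 | 0.28 |
| 40% | 40% | 15.0% | 25.0 | 2.5 | 1.3 | 0.08 |
| 40% | 50% | 8.3% | 41.7 | 4.2 | 2.1 | 0.22 |
| 40% | 60% | 1.7% | 58.3 | 5.8 | 2.9 | 0.44 |

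The last row is an extreme corner, because it leaves almost no inappropriate admissions from 30 weeks. With a gap of only 20 points, a 10-point difference shifts the contrast by 2 points.

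**3. How large a chance difference is plausible?** Assume also an intra-class correlation of 0.01-0.05 for presenting early.

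- SE of the arm difference in early share = √[s(1 - s) × (1 + 43.6 × ICC) × (1/267.7 + 1/312.3)].
- s = 30%, ICC 0.01: √(0.21 × 1.44 × 0.00694) = 4.6 points.
- s = 40%, ICC 0.05: √(0.24 × 3.18 × 0.00694) = 7.3 points.
- By the normal approximation, a difference above 5 points in either direction has probability 27-49%, and one above 10 points 3-17%.

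A 5-point difference is therefore ordinary, and 10 points is an adverse but credible case.

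**The case against.** Four stronger readings are tempting, and the document supports none of them.

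- *Gestation will not be adjusted for.* The words *such as* introduce examples, and gestation mix is itself a difference between cluster populations. The text shows only that gestation is not named.
- *Routine care before 30 weeks is treat-all.* Background reports guidance and an expectation: "most of these women are likely to be admitted". The section on in-utero transfer writes of a treat-all policy in the conditional, for some units. Neither describes observed control-arm practice.
- *The primary estimate is biased.* Chance imbalance under cluster randomisation does not bias the estimate in expectation. Outcome variation from differing gestation mix between centres is part of the between-cluster variance that the random effect and the ICC of 0.030 are meant to reflect. What is lost is precision and protection against an unlucky allocation.
- *A missing gestation subgroup is an error, because a verdict on treat-all is promised.* The Discussion sentence is conditional and states no 30-week limit; that limit comes from Background. The hypothesis concerns an overall reduction, which a pooled effect answers. Subgroup tables and full covariate lists may stand in an analysis plan that is not shown.

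Two things remain. The article did choose to describe its covariates, and what it describes is partly void (minimisation variables) and omits the one patient characteristic that it repeatedly connects with the decision. And if a conclusion about women before 30 weeks is drawn, the pooled effect over 23+0 to 34+6 weeks cannot carry it alone.

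**Conclusion.** The point holds as an improvement to the covariate set that costs almost nothing, plus one plain inconsistency: the model adjusts for variables from a minimisation that was not used. It is not a finding of bias, and the sample size stands.

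A 5-point arm difference in early presenters would move the contrast by about 1-3 points (7-19% of the planned 15). A 10-point difference would move it by 2.1-5.8 points (14-39%). For comparison, the planned standard error is about 4.8 points. Every one of these shifts rests on assumed gestation shares, gestation-specific rates and clustering of gestation, since the article gives none. The R² range of 0.05-0.44 rests on the same assumptions, is on a linear scale, and is only a rough guide to the precision that adjustment would recover in binomial regression.

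**What to change.** 1. In the Cluster randomised trial section, name gestation at presentation as a pre-specified covariate in the primary model, preferably continuous.
2. Replace the reference to minimisation variables with the actual, closed covariate list. If NICU level or threatened preterm labour rate was meant, say so.
3. If any conclusion about treating all women before 30 weeks is to be drawn, pre-specify the primary outcome by arm before 30+0 and from 30+0 weeks. Label it secondary and less precise, and rest the conclusion on it rather than on the pooled effect.

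The cost is one individual-level covariate, one edited sentence and, if the third step is taken, one extra table. Gestation is already collected at all sites, the sample size is unchanged, and no clinical rule is touched. The changes should be fixed before the unmasked data are analysed.

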#### Health economics evaluation

For the health economics analysis, a multi-level general linear model using appropriate family and link function, will be used to calculate the average cost per participant of use of the QUIPP app for triage and transfer compared to current practice. Costs will also be reported alongside secondary clinical outcomes as part of a cost-consequences analysis. We are not conducting a cost per quality adjusted life year (QALY) analysis (also called cost-utility analysis) given the hypothesis that the intervention is cost saving and does not result in any health decrement. These assumptions make a cost per QALY analysis redundant. Any health improvement will be captured by adverse incident reporting and secondary maternal and neonatal clinical outcomes, which will be reported alongside costs as part of the cost-consequences analysis.

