An health economics analysis will also be conducted; this will involve a cost-minimisation and cost-consequences analysis of the use of the QUIPP app for triage and transfer compared to current practice. We hypothesise that there will be no negative impact on the health and wellbeing of women and neonates, as a result of the intervention, particularly given its non-invasive nature and that the intervention will be cost saving.

Women’s experience of TPTL assessment will be explored using self-completed questionnaires, with a subset of participants being invited to semi-structured interview.

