### Sample size

For inappropriate admission decisions, a total sample size of 580, approximately 50 recruits per site, was calculated. Data from our group’s ongoing prospective observational study into the ability of qfFN to predict preterm birth in symptomatic women (PETRA REC Ref. 14/LO/1988) has allowed us to estimate the likely treatment effect for the intervention reducing inappropriate admissions from 25 to 10% and intra-class correlation 0.030. Based on 13 clusters this treatment effect requires approximately 580 for 80% power. We are aware that a larger number of centres would also be preferable, but believe 13 is adequate and at the limit of what is currently feasible.

For our qualitative questionnaires, we have estimated a target recruitment of 300 participants, 25 recruits per site, allowing for non-compliance and data collection errors. Based on previous research involving visual analogue scale (VAS) scores [19], a total sample size of 272 was required at standard levels of significance (alpha = 0.05 two-sided) to achieve 90% power to detect a 10% difference in mean VAS scores between hospitals with and without the intervention.

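### The cost-minimisation analysis rests on an assumed absence of health decrement that the trial does not test and is poorly placed to support if serious harms are rare

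*Protocol article*

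**What the plan says.** All references are to the Protocol article.

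- **Trial design** describes the economic work: "this will involve a cost-minimisation and cost-consequences analysis of the use of the QUIPP app". It adds: "We hypothesise that there will be no negative impact on the health and wellbeing of women and neonates".
- **Health economics evaluation** gives the reason for having no cost-utility analysis: "given the hypothesis that the intervention is cost saving and does not result in any health decrement". The next sentence calls these points assumptions and says that they make a cost per QALY analysis redundant. The section then says: "Any health improvement will be captured by adverse incident reporting and secondary maternal and neonatal clinical outcomes", with those outcomes reported beside costs. It mentions improvement only.
- **Cluster randomised trial** (Data analysis) says that the analysis will estimate the size of effects and "test for statistical significance of any effects of the intervention on primary and secondary" outcomes. Binary endpoints get risk ratios with 95% confidence intervals; risk differences are promised for the primary endpoint only. No margin is stated.
- **Sample size** covers inappropriate admissions and the VAS anxiety score. No calculation concerns a maternal or neonatal harm.
- **Discussion** says that the study will determine the risks as well as the benefits of limiting management, so it treats harm as an open question.

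**The concern.** Comparing costs alone is valid only if health outcomes are at least no worse. The plan takes this from a hypothesis. In the tests that it applies to maternal and neonatal outcomes, no harm is the null hypothesis, and failing to reject a null does not establish it. Cost-minimisation needs decrement to be excluded to some stated degree, yet the text provides only for capturing improvement.

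The intervention may lead to admission, transfer or treatment being withheld from women assessed as low risk. The harms that matter are therefore women not admitted who deliver within 7 days, avoidable ex-utero transfers, and neonatal morbidity or death. The Abstract says that the findings will inform national guidelines. A conclusion of savings without decrement would carry weight there, so it should rest on evidence from the trial.

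**Working it through.** **Inputs from the article.** Design effect size and ICC: "reducing inappropriate admissions from 25 to 10% and intra-class correlation 0.030". Size: "Based on 13 clusters this treatment effect requires approximately 580 for 80% power". Allocation: "seven sites were allocated to one group and six to the other"; Trial design gives 6 control units, hence 7 intervention units.

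**Assumptions.** Two-sided 5% test (stated in the article only for the VAS calculation). Control-arm harm rate *p* from 1% to 10%, because none is given. ICC for harms from 0 to 0.03; only 0.03 is in the article, and it refers to inappropriate admissions.

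**Formulas.**
- Cluster size m = 580/13 = 44.6; design effect DE = 1 + (m − 1) × ICC.
- Effective numbers: n₁ = 6m/DE (control), n₂ = 7m/DE (intervention).
- SE = √[p₁(1 − p₁)/n₁ + p₂(1 − p₂)/n₂].
- Power from a non-central t with 13 − 2 = 11 df, non-centrality |p₁ − p₂|/SE, critical value 2.201.

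**Step 1: the plan's own figure.** At ICC 0.03, DE = 1 + 43.6 × 0.03 = 2.31, n₁ = 267.7/2.31 = 116.0 and n₂ = 312.3/2.31 = 135.3. For 25% versus 10%, SE = 0.0478, non-centrality = 0.15/0.0478 = 3.14, and power = 81.5%. This agrees with the stated 80%. A normal approximation gives 88.4%, so the t version is the closer match.

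**Step 2: chance of missing a doubling of harm, same method.**

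| Control rate → app rate | Missed, ICC 0 | Missed, ICC 0.03 |
|---|---|---|
| 1% → 2% | 85% | 91% |
| 2% → 4% | 74% | 86% |
| 3% → 6% | 64% | 81% |
| 5% → 10% | 44% | 71% |
| 10% → 20% | 12% | 46% |

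Example, 2% → 4% at ICC 0.03: SE = √(0.02 × 0.98/116.0 + 0.04 × 0.96/135.3) = 0.0213; non-centrality = 0.02/0.0213 = 0.94; missed 86%.

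For the 1% to 3% rows, a normal approximation gives 60% to 91%. A beta-binomial simulation with clusters of 45 and a cluster-mean t-test gives 66% to 94%. The choice of method does not change the conclusion.

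**Step 3: what a null result would leave open.** With a true rate of 2% in both arms, the 95% half-width for the risk difference is 2.201 × √[0.02 × 0.98 × (1/n₁ + 1/n₂)]:
- ICC 0: 2.201 × 0.01166 = 2.6 percentage points.
- ICC 0.03: 2.201 × 0.01772 = 3.9 percentage points.

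An estimate of exactly no difference would thus remain compatible with more than a doubling of a 2% harm. Only about 5.4 and 6.2 events would be expected in the two arms (2% of 268 and of 312), so these approximations are rough.

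**Step 4: if recruitment exceeds 580.** By the normal approximation at 3,000 women and ICC 0.03, a doubling from 1% is missed 88.5% of the time and from 3% 72.1%. At ICC 0 the figures fall to 39.5% and 2.3%. Extra women help only if clustering of harms is weak.

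**The case against.** The strongest reply is that the plan does not rely on cost-minimisation alone. The cost-consequences analysis reports maternal and neonatal outcomes, including neonatal death, beside costs. The data monitoring committee reviews adverse neonatal outcomes and may consider both arms in closed session. Adverse incidents are reported. The under-treatment components belong to the primary outcome and are also analysed singly. All of this stands: harms will be visible. None of it, however, sets a condition on the cost-minimisation conclusion.

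Several stronger readings are tempting, but the article does not support them:

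- *The plan will declare the app no worse whenever p > 0.05.* No such rule is written, and the Discussion allows that a treat-all policy may prove justified. The gap is that nothing prevents that reading.
- *No upper limit on harm will be available.* Risk ratios come with 95% confidence intervals; only a margin to judge them against is missing.
- *All other economic analysis is dismissed.* Only the cost per QALY analysis is called redundant.
- *The trial cannot detect harm at all.* At a 10% rate most doublings would be detected.
- *The 147 g birthweight difference in the Background is a benchmark for harm caused by the app.* It is a harm of steroid exposure with later delivery, which the app aims to reduce.

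It is also fair that a condensed article may leave margins to a fuller document, so the absence of one is not itself the error. The premise, and the conclusion drawn from it, are stated in the article.

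**Conclusion.** The point holds in a limited form. The article uses an assumed absence of decrement to justify cost-minimisation and to omit a QALY analysis, and its tests of difference cannot establish that absence.

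The size depends on harm rates that the article does not give. With 580 women in 6 versus 7 clusters and ICC 0 to 0.03, about 64% to 91% of doublings would be missed for harms of 1% to 3%. For more common harms the problem is much smaller, so no single miss rate should be quoted without its assumptions. The calculation is a cluster-level approximation; the planned model is binomial regression with a random effect.

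This should be corrected, but it does not threaten the primary comparison.

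**What to change.** In Trial design and Health economics evaluation:

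1. Name the already planned cost-consequences analysis as the main economic analysis.
2. Report cost differences beside cluster-adjusted risk differences with 95% confidence intervals for three harms: non-admission followed by delivery within 7 days, ex-utero transfer, and one named adverse neonatal outcome.
3. State that a non-significant difference will not be read as absence of decrement. Claim savings without decrement only if the upper confidence limits support it, preferably against a margin that the sponsor fixes before unmasking. A formal margin is desirable but optional.
4. Extend the sentence on capturing health improvement so that it covers improvement or decrement.

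The cost is wording and a few extra estimates from data already being collected. The downside is that, at about 580 women, the intervals may be too wide for the sponsor to claim that there is no health decrement.
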